### Mentoring structure and follow-up

A structured mentoring framework will be integrated throughout the programme:•Mentor–mentee ratio: 1:5.•Mode of mentoring: Hybrid (in-person during workshops and virtual follow-up via email or online platforms such as Microsoft Teams).•Frequency: Bi-weekly sessions post workshops.•Duration: 30–60 min per session.

Mentor responsibilities include:•Providing individualized feedback on writing tasks.•Guiding journal selection and submission processes•Supporting manuscript revision following peer-review feedback.

Mentee responsibilities include:•Timely completion of assigned writing tasks.•Revising drafts based on mentor feedback.•Active participation in mentoring sessions.

### Writing tasks and learning process

Each workshop will include structured writing assignments aligned with learning objectives:•Workshop 1: Drafting title, abstract, and manuscript outline.•Workshop 2: Writing introduction and methods sections.•Workshop 3: Completing results, discussion, and submission-ready manuscript.

Feedback Mechanism:•Written feedback will be taken from the participants after each workshop.

### Content coverage

The programme will include interactive sessions involving lectures, hands-on activities, and feedback, covering:•Scientific paper structure and writing style.•Abstract and title development.•Figures, tables, and referencing.•Manuscript preparation and submission.•Journal selection and editorial processes.•Peer review and revision strategies.•Publication ethics and misconduct.•Indexing, impact indicators, and editorial systems.

## Data analysis

Quantitative data will be analyzed using Jamovi 2.4.1 version. Descriptive statistics (mean, SD, frequency, and percentage) will summarize demographic data and baseline characteristics.

Inferential statistics:•Paired *t*-test will compare pre- and post-test scores within groups.•Repeated measures ANOVA will compare mean differences between groups, controlling for baseline values.•The Cochran Q test will analyse categorical variables such as publication status.•Significance will be set at *p* < 0.05.

Qualitative data from FGDs will undergo thematic analysis following Braun and Clarke’s (2006) six-step approach: familiarisation, coding, theme development, reviewing, defining, and reporting. The integration of quantitative and qualitative findings will be performed to provide a comprehensive understanding of the barriers, facilitators, and impact of the intervention.

Furthermore, the effectiveness of the workshop-based intervention will be evaluated by comparing means of knowledge, attitude, publication efficacy, and publication status before and after the workshop using *t*-tests, allowing for an assessment of any significant changes resulting from the intervention. This comprehensive data analysis approach aims to provide a thorough understanding of the factors influencing research publication among nurse researchers and the impact of the intervention on key outcomes.

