In Phase II, eligible participants (*n* = 100) will be randomly assigned to either an intervention (*n* = 50) or a control group (*n* = 50). The intervention group will participate in the MWRP, comprising three workshops conducted over a four-month period. The control group will receive no intervention during this period. Pre- and post-assessments will be conducted for both groups at baseline, as well as at four- and six-month post-intervention.

All data will be coded anonymously, stored securely, and accessible only to the principal investigator.

Recruitment and Allocation Procedures.

Participants for Phase I will be recruited from nursing institutions across Karnataka through official communication with institutional heads and dissemination of study information via email and professional networks. Eligible nurse researchers who meet the inclusion criteria and provide informed consent will be enrolled in the survey. Participants for focus group discussions will be purposively selected from survey respondents to ensure diversity of experiences and perspectives.

For Phase II, participants will be recruited from Phase I respondents who indicate willingness to participate in the Mentored Writing Retreat Programme (MWRP) and meet the predefined eligibility criteria. After obtaining informed consent, eligible participants will be enrolled and assigned unique identification codes.

Given the quasi-experimental design, participants will be allocated into intervention and control groups using a non-randomized approach. Allocation will be based on feasibility and participant availability, ensuring comparable group sizes (*n* = 50 per group). Efforts will be made to maintain baseline comparability between groups by considering key characteristics such as academic qualification, prior publication experience, and institutional affiliation.

The intervention group will receive the MWRP, while the control group will continue with routine academic activities without structured intervention during the study period. To ensure ethical fairness, the control group will be provided access to the training materials after completion of the study.

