### Limitations

•The quasi-experimental design may not fully eliminate external factors influencing changes in publication-related outcomes, which could affect the internal validity of the protocol.•The protocol relies on self-reported measures of knowledge, attitudes, and publication efficacy, which may be subject to social desirability or recall bias.•The protocol is designed for nursing institutions in South India; therefore, its applicability to other regions or disciplines may be limited.•Participant engagement and completion of manuscript tasks may vary based on workload, motivation, and competing academic responsibilities, potentially affecting the overall effectiveness of the intervention.

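### The between-group model adjusts for baseline values only, although groups are formed without randomisation and the protocol names qualification, publication experience and institution as key to comparability

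*Protocol article*

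**What the plan says.** Allocation is described under Recruitment and Allocation Procedures (within the section Research publication manual): "participants will be allocated into intervention and control groups using a non-randomized approach". The basis is then given: "Allocation will be based on feasibility and participant availability, ensuring comparable group sizes". On comparability the text says: "Efforts will be made to maintain baseline comparability between groups by considering key characteristics such as academic qualification, prior publication experience, and institutional affiliation". It describes no matching, stratification or minimisation.

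Earlier in the same section, another sentence says that eligible participants "will be randomly assigned to either an intervention" or a control group. The abstract, the specifications table, the Phase 2 design description and the Limitations all call the design quasi-experimental.

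In Data analysis, the one method stated for comparing groups is: "Repeated measures ANOVA will compare mean differences between groups, controlling for baseline values". The t-tests are described as pre-post comparisons. For publication status the plan is: "The Cochran Q test will analyse categorical variables such as publication status". Descriptive statistics "will summarize demographic data and baseline characteristics", and no test is said to use those characteristics. The Limitations section concedes: "The quasi-experimental design may not fully eliminate external factors influencing changes in publication-related outcomes".

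**The concern.** In a non-randomised comparison, the adjustment set carries much of the weight of the effect estimate. The protocol singles out three characteristics as relevant to whether the groups are alike, does not guarantee balance on them, and then leaves them out of the only between-group model.

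Adjusting for the pre-test score removes the part of an imbalance that this score carries. It does not remove the rest. Suppose, for example, that participants at PhD level or with earlier publications gain more from pre-test to post-test than others with the same starting score. If one group holds more such participants, the extra gain appears as an effect of the writing programme. The p-value takes no account of this.

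**Working it through.** **1. What enters each test in Data analysis**

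| Method | Comparison | Covariates stated |
|---|---|---|
| Paired t-test, and the closing t-tests | before against after | none |
| Repeated measures ANOVA | between groups | baseline values |
| Cochran Q | related samples | none possible |
| Descriptive statistics | none | not applicable |

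None of the three named characteristics appears in any row.

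**2. Size of the possible error**

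From the protocol: 50 per group, two-sided 5% level (z = 1.96). Assumed, because the protocol gives neither figure: a binary factor with overall prevalence 50%; its effect g on the outcome that remains after baseline adjustment, 0.5 to 0.8 within-level SD; and the difference D in its prevalence between groups, 0.10 to 0.30.

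- Bias with no programme effect = D × g.
- SE = √(2/50) × √(1 + 0.25 g²). This is 0.206 for g = 0.5 and 0.215 for g = 0.8.
- Error rate = Φ(−1.96 + bias/SE) + Φ(−1.96 − bias/SE).

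| D | g | Bias (SD) | Error rate |
|---|---|---|---|
| 0.10 | 0.5 | 0.05 | 5.7% |
| 0.10 | 0.8 | 0.08 | 6.6% |
| 0.20 | 0.5 | 0.10 | 7.7% |
| 0.20 | 0.8 | 0.16 | 11.5% |
| 0.30 | 0.5 | 0.15 | 11.2% |
| 0.30 | 0.8 | 0.24 | 20.0% |

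**3. Does the pre-test score absorb it?**

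This was simulated with 3,000 runs per setting, 50 per group, no programme effect and D = 0.20. The factor was worth 0.5 on the pre-test, where the within-level SD of a score is about 1.

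| Factor effect on post-test | Pre-test only: bias, error rate | Pre-test plus factor: bias, error rate |
|---|---|---|
| 0.5 | 0.05, 6.2% | 0.00, 5.3% |
| 0.8 | 0.10, 7.9% | 0.00, 5.0% |
| 1.0 | 0.14, 10.0% | −0.01, 5.3% |

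The pre-test score absorbs part of the imbalance but not all of it. Adding the factor removes the remainder to within simulation error.

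**4. Precision**

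With the factor exactly balanced, the simulated SE was 0.173, 0.180 and 0.187 with the pre-test only, against 0.172 with the factor added. With D = 0.20 and the smallest effect, the order reversed slightly: 0.174 without the factor, 0.176 with it. A gain in precision is therefore possible but secondary.

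It cannot be turned into a power figure for this trial. The Phase 2 sample size formula with its own inputs gives 2.80² × 21.4² / 2.40² = 623 per group, not the stated 46. With 50 per group, SE = 21.4 × √(2/50) = 4.28 and 2.40/4.28 = 0.56, so two-sided power is about 8.7%. If covariates explained a further 10% to 20% of the variance, power would be 9.1% to 9.6%, a gain of less than one point.

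**The case against.** **The allocation may be random.** One sentence says so, and on that reading only the secondary precision argument would remain. The detailed allocation text and every description of the design point the other way, so the non-random reading is better supported. The contradiction still has to be resolved.

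**The wording on baseline values may be broader than the pre-test score.** It is not defined, and it closely follows a sentence on baseline characteristics. The pre-test score is the natural reading. If more was meant, the text needs the same clarifying sentence.

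**Covariate lists belong in a fuller plan.** This often holds for a journal article. Here, though, the article states the model and what it controls for, and that statement does not match its own allocation section.

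**The assumed sizes are unfavourable.** This stands in part. An effect of 0.5 to 0.8 SD left after baseline adjustment is large, and at a 10-point imbalance the error rate barely moves. With 50 per group and 50% prevalence, the chance SE of a prevalence difference is √(2 × 0.25/50) = 0.10, so 20 points would be a two-SE event (p about 0.046) under random allocation. Allocation by availability, however, is not bound by chance.

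**Stronger readings to avoid.** A reader might infer that the groups are formed by balancing on the three factors, or that the protocol calls them confounders. It does neither: allocation rests on feasibility and availability, and the three are examples of characteristics to be considered. A reader might also infer that publication history is ignored throughout. In fact publication status is measured at pre-test in both groups and, as a count of manuscripts, overlaps with prior publication experience. Finally, a reader might expect adjustment to lift power noticeably above the stated 80%. That figure does not follow from the protocol's own inputs, so no such gain can be claimed.

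**Conclusion.** The point holds as a mismatch between two stated parts of the protocol. Allocation is described as non-random with comparability not guaranteed, and the single between-group model omits the characteristics named as key to comparability. Any imbalance on them beyond what the pre-test score carries would be read as programme effect.

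Neither the direction nor the size of the bias can be derived from the protocol. Under the assumptions shown, the error rate runs from about 6-7% at a 10-point imbalance, through 8-12% at 20 points, to 11-20% at 30 points. The inflation is small if the groups turn out nearly alike and material if they do not. The change should be made, because it is cheap and an adjustment set chosen after the data are seen is less credible. The failure of the sample size arithmetic is a separate matter, and the bias argument does not depend on it.

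**What to change.** In Data analysis, prespecify academic qualification (MSc, pursuing PhD, PhD) and prior publication experience (none, any) as covariates alongside the pre-test score in the between-group model for knowledge, attitude and publication efficacy. Enter institution as a random intercept where feasible, or as a coarse grouping if most institutions contribute only one or two participants. State that the conclusion on effectiveness rests on this adjusted estimate, and report the unadjusted one beside it.

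For publication status, no between-group model is stated, and Cochran Q compares related samples. Once such a model is specified, apply the same covariates to it.

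Reconcile the sentence on random assignment with the non-randomised allocation text.

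The cost is a sentence or two and about 3 to 5 degrees of freedom out of roughly 90 to 100. No new data should be needed, since the characteristics are to be considered at allocation. The adjustment does not remove confounding by availability or motivation, and the report should say so.

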**Sample size.**

**Phase 1:** The sample size for survey was calculated using the single population proportion formula,$$n=\frac{{\left(Z_{1-\frac{\alpha }{2}}\right)}^{2}pq}{{\left(d\right)}^{2}}$$

$Z_{1-\frac{\propto }{2}}$ = 1.96 at α = 0.05, *p* = Proportion, q = 1-p, d = allowable error (5% of p).$$n=\frac{{\left(1.96\right)}^{2}x\;\;0.61\left(1-0.61\right)}{{\left(.03\right)}^{2}}=317$$

Focus group discussions (FGDs) will be conducted until data saturation is achieved.

**Phase 2:** The sample size was derived using the formula for two independent groups,$$n=\frac{{\left(Z_{1-\frac{\alpha }{2}}+Z_{1-\beta }\right)}^{2}\sigma^{2}}{d^{2}},$$

$Z_{1-\frac{\propto }{2}}$ = 1.96 at α = 0.05, $Z_{1-\beta }$ = 0.84 at 80% power.

σ = Standard deviation difference of knowledge scores. d = Difference in pre- and post-intervention mean scores of knowledge.

The expected mean differences (d₁ = 2.26 and d₂ = 2.55) were derived from pilot observations conducted during preliminary implementation of similar training sessions.

To ensure a conservative and robust estimate, the average of the two values was considered for calculation:$$d=\frac{2.26+2.55}{2}=2.40$$

The pooled standard deviation was calculated using: $\sigma =\sqrt{\frac{\sigma_{1}^{2}+\sigma_{2}^{2}}{2}}$where:$$\sigma_{1}=20.7,\;\;\sigma_{2}=22.1\;\sigma =\sqrt{\frac{{\left(20.7\right)}^{2}+{\left(22.1\right)}^{2}}{2}}\approx 21.4$$

Substituting values into the formula:$$n=\frac{{\left(1.96+0.84\right)}^{2}\times {\left(21.4\right)}^{2}}{{\left(2.40\right)}^{2}}$$

The calculated sample size was 46 participants per group (*n* = 46), and an attrition rate of 10%, the required sample size per group is approximately 50 participants.

A total of 100 nurse researchers (50 in each group) who met the inclusion criteria were included in the second phase of the study.

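### On the single post-test schedule, the named repeated-measures ANOVA does not adjust for baseline as the plan says, and it makes no allowance for shared mentors; name a baseline-adjusted model

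*Protocol article*

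**What the plan says.** Under Data analysis, the only between-group test named for the score outcomes is this: "Repeated measures ANOVA will compare mean differences between groups, controlling for baseline values". No covariate, tested term or time point is given. Within-group paired t-tests are listed beside it. A later paragraph of the same section says effectiveness will be judged by comparing knowledge, attitude, publication efficacy and "publication status before and after the workshop using *t*-tests".

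The assessment schedule is stated in more than one way. Programme structure and timeline has one post-test of knowledge, attitude and efficacy, in month 5, and publication status in month 10. The text that follows the manual's table instead has both groups assessed at baseline and at four and six months after the intervention. The Study design section confirms that pre-tests are taken in both groups.

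Mentoring structure and follow-up fixes "Mentor–mentee ratio: 1:5", with individual feedback from the mentor. Controls have no mentors.

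On allocation, one sentence assigns the 100 participants at random. A few paragraphs later, Recruitment and Allocation Procedures describes a non-random approach driven by feasibility and availability, with comparability sought by "considering key characteristics such as academic qualification, prior publication experience, and institutional affiliation".

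**The concern.** The analysis sentence promises adjustment for baseline. On the month-5 schedule the named method does not provide it. With two occasions, the pre-test score is one of the two outcomes in a repeated-measures ANOVA. The group-by-time term is then identical to a t-test on change scores. The group main effect compares the average of pre and post, which halves any programme effect. Neither conditions on the baseline score.

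Three things are at stake. The first is precision: under random allocation the change score is less precise than ANCOVA on the same data. The second is interpretation: if the groups differ at baseline, as they may when allocation follows availability, the change score and the adjusted analysis can give different answers, and the plan does not say which one decides. The third is the error rate: participants who share a mentor are likely to be correlated, and treating them as independent makes the intervention arm's standard error too small.

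**Working it through.** **The plan's own figure.** The Sample size section uses a two-sided test ("1.96 at α = 0.05"; "0.84 at 80% power"), difference 2.40 and pooled SD 21.4. Its formula gives 2.80² × 21.4² / 2.40² = 7.84 × 457.96 / 5.76 = 623 per group. The stated figure is 46, so it does not reproduce. That is a separate fault, but it means the printed inputs cannot be taken as they stand to size the present point.

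**Inputs.** From the protocol: two-sided α 0.05; 50 per group less 10% attrition = 45; five mentees per mentor, so 50/5 = 10 mentors, in one arm only. Assumed, because the protocol gives neither: pre-post correlation ρ of 0.3, 0.5 and 0.7, and mentor ICC of 0.05 and 0.10. Also assumed: effect 1.4 and SD 2.41. These are not the protocol's labelled values. They arise if its printed means and SDs were exchanged: 22.1 − 20.7 = 1.4 and √((2.26² + 2.55²)/2) = 2.41. Then 2 × 7.84 × 2.41² / 1.4² = 46.5, close to the stated 46. That is conjecture.

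**Variance per participant (SD = σ), one post-test, random allocation.**
- Change score (group-by-time): 2σ²(1 − ρ)
- ANCOVA: σ²(1 − ρ²)
- Ratio, ANCOVA to change score: (1 + ρ)/2 = 0.65, 0.75, 0.85 at ρ = 0.3, 0.5, 0.7

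**Power before clustering** (noncentral t, 88 df; noncentrality = 1.4 / (SD × √(2/45))). At ρ = 0.5, the change-score SD is 2.41 × √1 = 2.41, noncentrality 2.76. The ANCOVA SD is 2.41 × √0.75 = 2.09, noncentrality 3.18.

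| ρ | Change score | ANCOVA |
|---|---|---|
| 0.3 | 63% | 82% |
| 0.5 | 78% | 88% |
| 0.7 | 94% | 97% |

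**Same comparison at the printed inputs** (2.40, 21.4 as the SD of a single score, 46 per group, normal approximation): 6.6% to 8.1%, 7.7% to 9.0% and 10.3% to 11.4% at ρ = 0.3, 0.5, 0.7. The gain is about 1 point.

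**Mentor sharing.** The design effect in the intervention arm is 1 + (5 − 1) × ICC = 1.2 or 1.4. Averaged with 1 for controls, the variance of the difference rises by 1.10 or 1.20. If this is ignored, the effective critical value is 1.96/√1.10 = 1.87 or 1.96/√1.20 = 1.79, and the two-sided error is about 6.2% or 7.4%. Simulated ANCOVA without a mentor term (50 per group, 4,000 runs) gave 6.7% and 7.9%, so ANCOVA alone does not cure this. Once the sharing is allowed for, ANCOVA noncentrality at ρ = 0.5 is 3.18/√1.10 = 3.03 or 3.18/√1.20 = 2.90, and power is about 85% or 82%.

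**Non-random allocation.** If a baseline gap Δ between groups is stable over time, ANCOVA is biased by Δ(1 − ρ) and the change score is unbiased. With Δ = 0.3 SD and ρ = 0.5 the bias is 0.3 × 0.5 = 0.15 SD, and simulated false positives were 13.0% for ANCOVA against 4.7% for the change score. If the groups instead regress to a common mean, the change score is the biased one.

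**The case against.** Several parts of the opposing case stand.

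- A reader might infer that repeated-measures ANOVA can never control for baseline here. The documents do not support that. With post-tests at four and six months, a repeated-measures model of the two post scores with baseline as covariate would fit the analysis sentence. What can be said is that the text does not describe that model, and the month-5 schedule rules it out for knowledge, attitude and efficacy.
- A reader might infer that most of the power is lost, because the group main effect has only 35% power under the same assumptions at ρ = 0.5. But the sentence speaks of comparing mean differences, which points to group-by-time. The main effect is the least natural reading, and the realistic contrast is 78% against 88%.
- The 1.4 and 2.41 are not the protocol's labelled inputs, and at those the gain is trivial. However, an SD of 21.4 cannot belong to a single score on a 0–30 scale, where the maximum is about 15, so those figures are no better guide.
- ANCOVA is not assured to be the less biased method if allocation is non-random.
- The protocol gives a mentor ratio and does not say mentoring takes place in groups of five. Shared mentors are a fair inference, the ICC is assumed, and an analysis plan not shown may deal with clustering. This part is secondary.
- Loss of participants with a missing visit does not separate the methods: with one post-test, ANCOVA also needs both scores.

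**Conclusion.** The point holds in limited form. On the timeline's single post-test, the claim to control for baseline is not met by the named test; on the alternative schedule it could be, but the model is not stated. This is a fault in the wording of the plan and not merely a detail left for later, because the sentence attributes to the method something it does not do on one of the plan's own schedules.

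The direction of the efficiency gain follows from (1 + ρ)/2 being below 1 for any ρ below 1, provided allocation is random. Its size depends on unstated quantities: between 3 and 19 power points over ρ from 0.7 to 0.3 with the assumed effect and SD, and about 1 point at the printed ones. Under non-random allocation the case for ANCOVA as sole analysis is weaker, and the two analyses should be shown together. The understatement of error from shared mentors is modest at the ICCs assumed and needs its own correction.

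**What to change.** 1. Name one primary between-group analysis: post-test score regressed on group and baseline score (ANCOVA), adjusted for qualification and prior publication, at a stated time point. Report the adjusted difference with a 95% confidence interval.
2. Reconcile the assessment schedules. If both post-intervention visits apply to the scores, use a linear mixed model of the post scores with baseline as covariate.
3. In the intervention arm only, add a random mentor effect or a cluster-robust variance; controls stay unclustered.
4. Reconcile the random and non-random allocation statements. If allocation is non-random, report the change-score (group-by-time) result as a sensitivity analysis and say why the two may differ.
5. Make clear that the before/after t-tests are descriptive and do not decide effectiveness.

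No new data are needed beyond a record of which mentor each participant had. The cost is wording and slightly more modelling. The downside is that the mentor variance rests on about ten mentors, so intervals widen a little. The sample-size calculation needs separate correction with a checked SD; this change does not repair it.

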**Fig. 1 fig0001:**
[figure not shown]
Framework of MWRP.

The development and implementation of the MWRP will follow four iterative PAR cycles:•Plan: Identification of barriers and facilitators through surveys and focus group discussions.•Act: Development and implementation of the MWRP and research publication manual.•Observe: Monitoring participant progress, engagement, and outcomes during workshops and mentoring.•Reflect: Evaluation of feedback from participants and mentors to refine workshop content, mentoring strategies, and delivery methods.

Each cycle will inform subsequent modifications, ensuring that the programme remains contextually relevant, responsive to participant needs, and continuously improved.

*Phase 1: Exploratory Survey on Barriers and Facilitators for Research Publication.*

Phase I of the study is structured as an explorative investigation aiming to identify the barriers and facilitators for research publication as perceived by nursing professionals employed in nursing institutions. This phase employs a combination of methods, including a descriptive survey and focus group discussions.

The primary objective of Phase I is to gain insights into the challenges and supportive factors encountered by nursing professionals in the process of publishing research findings. Through the descriptive survey, participants will provide valuable information regarding their experiences, perceptions, and the various obstacles hindering or facilitating their engagement in research publication activities.

Additionally, focus group discussions will be conducted to delve deeper into the identified themes and gather rich qualitative data. These discussions will offer a platform for participants to express their perspectives, share experiences, and offer suggestions for overcoming barriers to research publication.

The findings from Phase I will serve as a foundation for informing the development and implementation of interventions aimed at enhancing the research publication process among nurse researchers.

*Phase 2: Impact of Mentored Writing Retreat Programme (MWRP).*

In Phase II, the study shifts focus towards evaluating the impact of the Mentored Writing Retreat Programme (MWRP) on optimizing the research publication process among nurse researchers. This phase adopts a quasi-experimental design, specifically employing a Pretest-Posttest approach with both control and interventional groups.

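### The effectiveness conclusion is tied to before-after t-tests that do not use the control group, although a between-group analysis is also planned; publication status has no clear between-group test

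*Protocol article*

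**What the plan says.** Phase II has a control arm by design, "specifically employing a Pretest-Posttest approach with both control and interventional groups" (Design framework, Phase 2). The data collection text adds: "The control group will receive no intervention during this period". Both groups are assessed at the same times.

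The Data analysis section lists three inferential methods:

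- A paired t-test, which "will compare pre- and post-test scores within groups".
- A controlled analysis: "Repeated measures ANOVA will compare mean differences between groups, controlling for baseline values".
- A method for categorical outcomes: "The Cochran Q test will analyse categorical variables such as publication status".

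The closing paragraph of the section then returns to t-tests. It says the "effectiveness of the workshop-based intervention will be evaluated by comparing means of knowledge, attitude, publication efficacy, and publication status before and after the workshop", and describes this as "allowing for an assessment of any significant changes resulting from the intervention". This is the only sentence in the section that says how effectiveness is to be evaluated.

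**The concern.** A mean change from before to after in one arm combines the programme effect with everything else that moves over the period: sitting the same questionnaire again, and ordinary progress on a manuscript. Phase II participants are chosen for wanting to publish and to prepare manuscripts, and controls carry on with routine academic work, so some improvement without the programme is plausible in both arms. The control group is there to remove that part, and a before-after t-test leaves it in.

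The plan therefore offers two bases for the same conclusion, does not rank them, and attaches the causal wording to the weaker one. An ineffective programme could be reported as effective on the wording as it stands. Publication status, the outcome closest to the study's aim, is worse placed, because neither method named for it clearly compares the groups.

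**Working it through.** **What the plan's figures offer.** The protocol gives no expected retest gain and no usable SD of change. Its printed inputs (Sample size, Phase 2) are SD 21.4 and difference 2.40. In the printed formula they give (1.96 + 0.84)² × 21.4² / 2.40² = 7.84 × 457.96 / 5.76 = 623, not the stated 46. That is a separate defect, and nothing below depends on it, but it means the printed SD is not a safe input. Knowledge is scored 0–30, so the SD of a raw score cannot exceed about 15. A change score could in theory reach 21.4, but only if people moved across most of the scale in opposite directions.

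**Inputs for the illustration.**

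- Completers per group: 50 × 0.90 = 45 (protocol: 50 per group, 10% attrition).
- Two-sided α = 0.05, critical t on 44 df = 2.015.
- True programme effect: zero.
- Gain shared by both groups: 1.0 or 1.5 points (assumption).
- SD of change: 3, 4 or 5 points (assumption), and 21.4 as printed.

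**Before-after test in the programme arm.** The noncentrality is gain / (SD / √45). For a gain of 1.0 and SD 4 it is 1.0 × 6.708 / 4 = 1.68. The chance of significance is P(|T| > 2.015), with T noncentral t on 44 df.

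| SD of change | Gain 1.0 | Gain 1.5 |
|---|---|---|
| 3 | 59% | 91% |
| 4 | 37% | 69% |
| 5 | 26% | 50% |
| 21.4 (printed) | 6% | 7% |

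Two other SDs can be tied to the protocol's own numbers, with 46 per group. If 21.4 is read as a variance, the SD is √21.4 = 4.63, and a 1.0-point gain gives 30%. The SD at which the printed formula would return 46 is √(46 × 5.76 / 7.84) = 5.81, and a 1.0-point gain gives 21%.

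**Between-group test of change, same setting.** The shared gain cancels in the difference, so under normality the rate is 5% by construction. In 20,000 simulated trials per setting (45 per group, all SDs and gains in the table) it was 4.7% to 5.3%.

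**Publication status.** The protocol defines it as the number of manuscripts completed, submitted or published.

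- The t-test named for it is before versus after.
- Cochran's Q compares related binary measurements in the same people and does not contrast two independent groups.
- If status is recorded cumulatively (assumption), it can only rise. With two time points Q = (b − c)² / (b + c), where b moved from no to yes and c from yes to no. With c = 0, Q = b, and the 5% limit is 1.96² = 3.84. Four people reaching the milestone for the first time would make the arm's test significant, whatever happened among the controls.

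**The case against.** The strongest reply is that the controls are not ignored. The same section plans a between-group ANOVA with baseline control, both groups are measured together, and the closing paragraph is introduced as an addition to the listed tests, not a replacement. This stands. A reader might infer that the 50 controls contribute nothing to the trial's conclusions, and for knowledge, attitude and efficacy the documents do not support that.

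A reader might also infer a decision rule: that one significant within-group test, or significance in one arm but not the other, counts as success. The protocol states no such rule.

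The size depends on assumed gains and SDs, and at the printed SD the inflation is slight. This also stands, so the percentages are an illustration and not an estimate for this trial.

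Four outcomes are tested at 0.05 with none named as primary in the analysis. Outcome hierarchy and multiplicity control are commonly left to a statistical analysis plan that is not shown. Phase II is already sized on knowledge, and a Holm adjustment would be a preference.

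The reply does not remove the sentence itself. It says how effectiveness will be evaluated, names a method that cannot isolate the programme, and reads the result causally. Nor does the ANOVA bullet clearly reach publication status, which is assigned to Cochran's Q and the t-test.

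**Conclusion.** The concern holds in this form. The plan contains a suitable controlled analysis for the three scale outcomes but ties the effectiveness conclusion to uncontrolled before-after t-tests on all four, and for publication status no between-group test is clearly specified.

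If the closing paragraph is followed, the false-positive rate for the question of whether the programme works depends on the size of the shared gain. With zero effect, 45 completers and a 1.0-point gain it is 26% to 59% for an SD of change of 5 to 3 points, and about 6% at the printed SD of 21.4. A between-group test of change stays near 5%. That last figure assumes both groups share the same gain, which is less secure if allocation is not random. The protocol describes allocation in one place as random and in another as non-randomized.

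**What to change.** - **Scale outcomes.** Rewrite the closing paragraph of Data analysis so that effectiveness for knowledge, attitude and publication efficacy is judged only by the baseline-adjusted between-group comparison: the group-by-time interaction, or ANCOVA on the post-test score with baseline as covariate. A bare post-test contrast would not do, because it drops the baseline control the plan already has.
- **Allocation.** Reconcile the two descriptions. If allocation is non-randomized, also adjust for the characteristics the protocol names for comparability: qualification, earlier publications and institution.
- **Publication status.** Replace Cochran's Q and the t-test with a between-group comparison adjusted for baseline status, such as logistic regression for any submission or publication, or a count model for the number of manuscripts.
- **Within-group changes.** Report them as means with confidence intervals and make no effectiveness claim from them.
- **Optional.** Name knowledge as the primary outcome, since Phase II is sized on it.

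The cost is wording and some analysis code, with no new data. The downside is fewer significant results to report.
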